### Procedure for unblinding if needed

Study is open-label, unblinded.

## Data collection and management

### Plans for assessment and collection of outcomes

Data collection for the efficacy analysis is planned at screening, baseline, and at 3-, 6-, 9- and 12-month follow-up assessments (Table 3). All participants will complete quantitative questionnaires in English and Spanish through the secure REDCap platform at baseline, and at 6- and 12-month follow-up assessments. Measures from NIDA’s Data Harmonization projects, specifically PhenX Toolkit [70], will be included. Assessments will take approximately 1 h and include socio-demographics, SUD treatment history, sexual and injection risk behaviors, substances used by injection and other routes of administration, and healthcare service utilization. Importantly, in pursuit of relevant endpoints important for people with SUD, quality of life measures [71, 72] will be assessed in addition to any changes in syndemic factors such as social determinants of health (e.g., employment, housing, food insecurity, incarceration) and mood (e.g., PHQ-9 [73], BAI [74]). We will use the EuroQol 5D (EQ-5D) to measure health-related quality of life [75, 76]. Stigma and discrimination will be measured using the Substance Use Stigma Mechanisms Scale (SU-SMS) [77], the Group-based Medical Mistrust Scale [78], the PrEP Stigma Scale [79], and Physician–Patient Relationship Scale [80].

**Table 3 Tab3:**
[figure not shown]
Assessment schedule

All participants will complete laboratory assessments at screening and at 3-, 6-, 9- and 12-month follow-up assessments. At screening, this will include rapid HIV test by fingerstick and point of care urine screens for tenofovir, buprenorphine, and methadone to determine eligibility. Additional tests at screening include fourth generation HIV test, HCV RNA, STI screens, hepatitis serologies, comprehensive metabolic panel, complete blood count and, as indicated, urine pregnancy test. At baseline and at 3-, 6-, 9- and 12-month follow-up assessments, these will include urine drug screen for buprenorphine/norbuprenorphine and methadone/EDDP (methadone metabolite) and fingerstick DBS to test for both the presence and therapeutic levels of TFV-DP related to the primary outcome, as well as HIV Ag/Ab screen, HCV RNA, HIV/HCV rapid tests, and STI screen (including syphilis via blood and gonorrhea/chlamydia via throat swab, rectal swab, and urine). Additionally, participants in the *C-THR* arm will also have a creatinine assessment at 6 and 12 months.

To confirm primary outcome by medical record abstraction, the electronic health record will be quieried for date of injection of (1) cabotegravir, (2) naltrexone or (3) buprenorphine. A cabotegravir injection in the previous 8 weeks will be considered as having met the primary outcome. A naltrexone or buprenorphine injection in the previous 4 weeks will be considered as having met the primary outcome.

The cost and cost-effectiveness analysis will consist of an economic evaluation of *C-THR* versus non-SSP clinic referral and patient navigation from both the healthcare sector perspective and the modified societal perspective. Specifically, the evaluation will focus on budgetary impact and cost-effectiveness to inform application of *C-THR* locally and nationally. This evaluation will follow recommendations of the 2nd Panel on Cost Effectiveness in Health and Medicine [45], Glick et al. [46] and Drummond [47].

Specifically, start-up and ongoing management costs related to the two strategies will be collected using macro-costing (“top down”) and micro-costing (“bottom up”) techniques using a tailored version of the Drug Abuse Treatment Cost Analysis Program (DATCAP) instrument [81], a standardized, customizable tool used to estimate costs of treatment in diverse settings. The macro approach is based on financial information received from the sites, such as invoices and time sheets, and the micro approach is based on semi-structured interviews with site leaders and staff, which will be conducted via site visits, video conferences, and phone calls to capture both accounting and economic costs. Financial information will be supplemented with healthcare utilization data from electronic health records and health system administrative databases and with semi-structured interviews with staff members, which will allow for the identification of other resources used to provide *C-THR* services. To perform a modified societal perspective analysis, data will be collected regarding criminal justice involvement during the trial. The REducing infections related to Drug Use Cost-Effectiveness (REDUCE) model [49] will be adapted and employed to project the long-term clinical and cost-effectiveness of the intervention at preventing incident cases of HIV over the 5-, 10-year, and lifetime horizons.

Finally, the implementation process evaluation will be mixed-methods using the Practical, Robust Implementation and Sustainability Model (PRISM) as the primary conceptual framework for guiding and evaluating the implementation efforts [82]. PRISM emphasizes the importance of multilevel contextual factors that act as drivers of implementation outcomes, such as the organizational and the patient perspective of the intervention, the external environment (i.e., community-level resources) and the implementation and sustainability infrastructure. PRISM was selected in part due to synergy with the RE-AIM evaluation framework [83].

PRISM and RE-AIM will inform both quantitative and qualitative data collection instruments focused on organizational-, provider-, and patient-level domains regarding the intervention based on constructs identified in the PRISM model; the relationship between these contructs and specific RE-AIM outcomes will also be evaluated. This information alongside the RCT will provide data needed to interpret a potential null effect of the intervention as a need for further intervention refinement or a failure of implementation. In addition, in-depth interviews with key informants (n = 20) within the Miami site and system (e.g., SSP staff, trial implementers, study physicians) at two distinct timepoints (at 6-months and trial closeout) will be conducted to assess organizational-level influences on Reach, Implementation, and Maintenance metrics. Additionally, 30 participants will complete qualitative assessments in English or Spanish at 12-month follow-up assessments. Participants will be asked about their experience engaging in the *C-THR* intervention, additional modifications needed to improve the intervention design, and additional strategies that could be used to increase the future reach of the intervention.

Interviews will be used to inform ongoing optimization and adaptations as the trial progresses. In addition to the set interview schedule, a review of trial logbooks and on-site observation data will be used to record strategies used and barriers encountered to enhance our evaluation efforts.

### Plans to promote participant retention and complete follow-up

Participants will be recruited from the IDEA Miami SSP by our racially and ethnically diverse staff that includes peer counselors. Due to the fundamental trust that the SSP has within the community of PWID, we anticipate that utilization of the harm reduction approach of meeting potential participants where they are will support ongoing recruitment into the trial due to the benefits of participation (including telehealth access to a physician, psychologist, counselor). Study staff are experienced and trusted in the community of PWID, and our empowerment of peers as the true experts in PWID health will facilitate recruitment. Providers can remain permanent after trial conclusion since stigmatization continues to be omnipresent in the traditional healthcare system. In our *THR* for PWID with HIV pilot (n = 35), all PWID continued to receive HIV primary care via *THR* after the pilot, even when no longer utilizing syringe services. Since all participants will be recruited via the SSP, the routine exchange of syringes and street outreach will ensure ongoing contact with all participants in the trial. Participants typically visit the program weekly and this ongoing distribution of harm reduction supplies will allow the study team to retain participants in the trial. In CTN-67 CHOICES, of 47 randomized patients with HIV and OUD at the University of Miami site, we retained 45 (96%) at 12-month follow-up. We also plan to use a locator form that we have used in other CTN studies and that will be reviewed by our community advisory board. Based on previous published studies regarding HIV prevention among PWID and to ensure we obtain adequate power to detect an effect, we have powered the trial for 12-month retention rates of 66%.

### Data management

A study-specific data management protocol and standard operating procedures will guide the study team throughout the trial. All data management activities will utilize REDCap, which is secure, HIPAA compliant, and web-based and has real time validation rules at the time of entry. The lead statistician will provide ongoing oversight of data management throughout the study and oversee the data manager in generating regular reports for quality control and data analysis. A study-specific data dictionary will be developed by all members of the research team. Data management reports will be made to the Data and Safety Monitoring Board (DSMB). Cleaned, de-identified data files will be produced for analysis.

### Confidentiality

All data will be kept confidential, electronically locked via password, and available only to authorized staff. The passwords will change periodically and accessible only to specified study staff. Participant data will be identified by an ID number only in the REDCap database. The link between names and ID numbers will be kept separately under password protection that only the site PIs can access*.* Participant case management files (including consents for third party pickup of medications, consents for medication storage, and locator forms) will be locked in a secure file cabinet in a room accessible by keycard and monitored by University of Miami Security.

All participants will be advised that they may decline to answer any study question. These procedures will be implemented to provide study participants with the assurance of confidentiality around sensitive and personal information relating to their mental health, sexual and substance use behaviors, and HIV status. All study personnel working on the project will be trained in human subjects research, good clinical practice, and the importance of strictly respecting participants' rights to confidentiality.

### Plans for collection, laboratory evaluation and storage of biological specimens for genetic or molecular analysis in this trial/future use

The primary and secondary outcomes for objective 1 will be measured with TFV-DP on fingerstick DBS, buprenorphine/norbuprenorphine or methadone/EDDP (methadone metabolite) on UDS, HIV Ag/Ab screen, HCV RNA, HIV/HCV rapid tests, and STI screen (including syphilis via blood and gonorrhea/chlamydia via throat swab, rectal swab and urine). These laboratory assessments will be completed as routine blood, urine, and throat and rectal swab lab tests, sent to a commercial laboratory or Florida Department of Health, and destroyed according to their procedures.

## Statistical methods

### Statistical methods for primary and secondary outcomes

#### Preliminary analyses and missing data

Frequency tables for all variables and measures of central tendency and variability for continuous variables will characterize the sample and be stratified by randomization group (i.e., intervention vs. control). As recommended by CONSORT guidelines (http://www.consort-statement.org/), we will not do statistical tests comparing randomized groups at baseline. Our primary analyses will need to control for any measured characteristics that predict missing data. Thus, in a preliminary analysis we will examine whether any baseline characteristics predict the pattern of missing data observed in the trial. All important predictors from this analysis will be included as control variables in the primary tests of hypotheses. In addition, for our moderator (and mediator) hypotheses, there may be some missing data on self-reported syndemic factors, for example. We will address any incomplete data with multiple imputation [84], full-information maximum likelihood or the expectations-maximization algorithm, all of which make the relatively mild assumption that incomplete data arise from a conditionally random (MAR) mechanism [85–87]. Auxiliary variables will be included to improve efficiency and any potential bias [88, 89]. The proposed analyses will be conducted using validated algorithms in SAS [90] or Mplus [91]. All program code and results will be documented extensively and archived to enable future review, transparency, and results reproducibility.

##### *Hypothesis 1*

*C-THR* will be superior to non-SSP clinic referral and patient navigation in promoting engagement in HIV prevention as measured by the proportion of participants taking PrEP and/or MOUD across follow-up at 3, 6, 9 and 12 months post-randomization.

### Primary inferential analyses to address primary hypothesis of objective 1

We hypothesize that, for those randomized to the *C-THR* arm, the odds of our two co-primary outcomes, engagement in PrEP and engagement in MOUD, will be higher than for those randomized to the non-SSP clinic patient navigation, control arm (Hypothesis 1). Generalized estimating equations (GEE) [92] will be used to perform the proposed primary analysis, which is a planned time-averaged comparison of all post-baseline measurements of the each of these outcomes—PrEP: DBS evidence of tenofovir or cabotegravir injection in the previous 8 weeks by electronic health record abstraction; MOUD: UDS with norbuprenorphine or methadone/EDDP; or naltrexone or buprenorphine injection in previous 4 weeks by electronic health record abstraction—across the *C-THR* and control groups to test primary Hypothesis 1. Alpha will be set at 0.025 for this planned comparison to control the Type-1 error across these two co-primary outcomes. In each model, recruitment site (fixed site vs. mobile site) and OUD diagnosis (yes vs. no) will be included in these analyses as required by the stratified randomized design to obtain unbiased results. If the overall test of the intervention is statistically significant, individual contrasts for differences between the conditions at each of the times of follow-up will be performed.

Though GEE estimates are consistent even if the correlation structure is misspecified, GEE's statistical efficiency improves as the working correlation structure more closely approximates the actual correlation structure [92], so various correlation structures suitable for the study's design will be considered (e.g., exchangeable, autocorrelated, *m*-dependent, unstructured) [93]. The QIC statistic will be used to select the final correlation structure [94]. Recruitment site (fixed site vs. mobile site) and OUD diagnosis (yes vs. no) will be included in all models as required by the stratified randomized design to obtain unbiased results [95]. Robust standard errors will be used to obtain correct inferences even if the chosen correlation structure remains slightly mis-specified. All analyses will include outlier and influential case screening via computation of GEE-based residual analysis, including leverage, DFBeta, and Cook’s D statistics [96]. If outliers are found, results will be reported with and without outliers included.

### Data analysis plan and statistical procedures to address secondary hypotheses of objective 1

We have proposed several secondary hypotheses related to the *C-THR* intervention. The secondary analyses will use exactly the same preliminary analysis and missing data strategy as Hypothesis 1. In secondary analyses, we will examine the distributions of syringe coverage, PrEP adherence, HCV treatment engagement, HCV cure, STI treatment uptake, and number of injection related harms and assess time to first injection-related harm between the intervention and control groups. GEE [92] will be used to perform the proposed secondary analysis, which is a planned time-averaged comparison of all post-baseline measurements of the each of these outcomes. Statistical procedures for these secondary hypotheses will follow the same strategy used for the primary hypothesis. The alpha will be set at 0.05 for each these secondary hypotheses. In each model, recruitment site (fixed site vs. mobile site) and OUD diagnosis (yes vs. no) will be included in these analyses as required by the stratified randomized design to obtain unbiased results. To maximize rigor, appropriate diagnostics including outlier and influential case screening will be examined for each model. If outliers are found, results will be reported with and without outliers included.

The count of harms will be assessed in a similar fashion as the analysis of the secondary hypotheses except that the distribution will be either a Poisson or Negative Binomial (the Negative Binomial will be used if overdispersion is present) and the link function will be log. For time to first harm, the comparison will be made using the logrank test and Kaplan–Meier estimates of the survival curve.

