PWID often experience pervasive discrimination, stigma, degradation and social disadvantage when accessing the traditional healthcare system, leading to almost universal poorer health outcomes compared to non-PWID [9–17]. However, one long-standing, trusted, and frequented institution for PWID are SSPs. Decades of research have highlighted their effectiveness in HIV prevention [18–23] and, more recently, their ability to implement HIV testing [24], PrEP [25], medications for opioid use disorder (MOUD) [26], and overdose education and naloxone distribution [27]. Increased access to MOUD has been shown to facilitate positive care outcomes among people with opioid use disorder (OUD) [28, 29], and SSPs have been shown to be ideal venues to offer PrEP [30] and buprenorphine [31–33] to further mitigate HIV risk and acquistion. However, initiating and retaining PWID on PrEP and MOUD remains a major implementation challenge, limiting our ability to meet Ending the HIV Epidemic targets. Multiple studies have demonstrated significant gaps in the PrEP cascade for PWID, leading to extremely low uptake, initiation, and persistence on PrEP (0–3%) [34–36]. Likewise, the OUD care cascade has pervasive gaps, with low rates of OUD screening, MOUD initiation, and MOUD retention among PWID [37]. Questions remain on how to most effectively implement sustainable and scalable integrated HIV prevention and OUD care models in SSPs for PWID.

We developed, refined, and pilot tested *tele-harm reduction (THR)*: a telehealth-based, multicomponent care model for PWID with HIV implemented at the IDEA Miami SSP. *THR* integrates multilevel stigma reduction [38, 39] and harm reduction frameworks [40] to provide access to HIV care through telehealth in an SSP setting that is supported by on-site peer-driven systems of care to enhance treatment initiation and adherence. *THR* has preliminarily demonstrated high acceptability and promising outcomes with 78% of PWID with HIV achieving viral suppression at 6 months post-enrollment, significantly higher than current national estimates which show 56.9% of PWID are virally suppressed [2, 40–42]. Our interdisciplinary research team is currently testing the efficacy of the *THR* model for HIV viral suppression in a randomized controlled trial (RCT) under a National Institute on Drug Abuse Avenir Award (DP2DA053720, PI: [name]).

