### Objectives

The first objective of the study is to compare the efficacy of the *C-THR* intervention for engagement in HIV prevention services (i.e., PrEP and MOUD) versus non-SSP clinic referral and patient navigation, with the co-primary outcome the time averaged proportion of participants engaged with PrEP or MOUD across follow-up at 3, 6, 9 and 12 months. For PrEP, engagement is confirmed by tenofovir on dried blood spot or cabotegravir injection within the previous 8 weeks. For MOUD, engagement is defined as screening positive for norbuprenorphine or methadone on urine drug screen (UDS); or extended release buprenorphine or naltrexone injection within the previous 4 weeks. The primary hypothesis is that C-THR will be superior to non-SSP clinic referral and patient navigation in promoting engagement of PWID in HIV prevention.

In relation to the primary objective, we will also measure differences between study arms in several secondary outcomes including syringe coverage, PrEP adherence, engagement in hepatitis C virus (HCV) treatment, rates of HCV cure, treatment of sexually transmitted infections (STIs), time to injection-related harm and number of injection-related harms. Participants in the C-THR arm will have peer-facilitated enhanced access to a physician via a telehealth platform, phlebotomy at both fixed and mobile sites, peer-facilitated medication management (e.g., storage in pill lockers at SSP, weekly delivery), appointment reminders, and mental health counseling. Participants assigned to the non-SSP clinic referral and patient navigation arm will be linked to a community health center or primary care clinic (e.g., Federally Qualified Health Center) by SSP staff as is the current standard of care with patient navigation for the first clinic visit.

The second objective of the study is to estimate the short- and long-term clinical- and cost-effectiveness of *C-THR* versus non-SSP clinic referral and patient navigation. The economic analysis will follow best practices for conducting economic analyses alongside clinical trials [45–47]. The long-term clinical and cost-effectiveness will utilze a validated simulation model [48, 49]. The REDUCE model was designed to simulate the natural history of IDU and understand how both hospital- and community-based interventions designed to *reduce* injection frequency and *reduce* risky injection behaviors (e.g., decrease needle reuse) may improve long-term outcomes.

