### Sample size

Power analyses were generated using the two-group repeated proportions module in PASS 2020 [68] to compute minimum detectable effect sizes for the proposed primary analysis. The study will include 350 participants equally assigned to the intervention and control groups. We assume that as much as 10% of the sample may drop-out at each follow-up; however, we anticipate better retention due to SSP staff engagement in the study [69]. The expected sample sizes at the four follow-ups are thus 315, 284, 255, and 230. Using these sample sizes and assuming α = 0.025, power = 0.80, and that the proportion with PrEP or MOUD engagement will be 30% of the control arm, we computed the minimum detectable odds ratio (OR) 1.56 and absolute proportion difference (pdiff) of 0.101, assuming that all post-intervention time points are part of the contrast. We varied the within-subject correlation ρ from 0.10 to 0.80. Power for a binomial is lowest when the base-rate (control group) probability (P_0_) is near 50%.

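### Hypothesis 1 is worded both as one combined PrEP-or-MOUD proportion and as two separately tested outcomes, and the single detectable effect (OR 1.56) is tied to neither test

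*Protocol article*

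**What the plan says.** **One combined outcome.** The Objectives section describes the first objective "with the co-primary outcome the time averaged proportion of participants engaged with PrEP or MOUD across follow-up": one outcome, one proportion. The line headed Hypothesis 1 says that superiority will be judged "as measured by the proportion of participants taking PrEP and/or MOUD across follow-up at 3, 6, 9 and 12 months post-randomization".

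**Two outcomes.** Under the primary inferential analyses for objective 1, the same hypothesis is that "the odds of our two co-primary outcomes, engagement in PrEP and engagement in MOUD, will be higher" in the C-THR arm. Each outcome is compared by a time-averaged GEE model, and "Alpha will be set at 0.025 for this planned comparison to control the Type-1 error across these two co-primary outcomes". Table 1 in the Outcomes section also lists PrEP and MOUD as separate primary rows, each with its own measure.

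**Sample size.** "The study will include 350 participants equally assigned to the intervention and control groups", and "We assume that as much as 10% of the sample may drop-out at each follow-up", which leaves 315, 284, 255 and 230 at the four visits. With alpha 0.025 and 80% power, the section assumes that "the proportion with PrEP or MOUD engagement will be 30% of the control arm" and reports a minimum detectable OR of 1.56 and a difference of 0.101. Within-subject correlation was varied from 0.10 to 0.80, but only one result is given. The section adds that power for a binomial is lowest when the control rate is near 50%.

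**PrEP rate.** No control rate is given for PrEP alone or MOUD alone. The only PrEP rate is in Background and rationale, on gaps in the PrEP cascade "leading to extremely low uptake, initiation, and persistence on PrEP (0–3" per cent).

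**The concern.** The primary claim can be read in two ways. A gain in MOUD with no change in PrEP, or a gain visible only in the combined proportion, would count as success under one sentence and not clearly under the other. Other rules inherit the ambiguity. The Interim analyses section bases its futility rule (conditional power below 0.5) on a single primary outcome without naming it. The per-visit contrasts are released by one overall test, although there are two. The sex interaction is written for one engagement outcome. In an open-label trial whose own investigators run the analysis, the wording should leave no choice to be made later.

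The sample size has the matching problem. A detectable odds ratio depends on the control rate. If 30% is the combined rate, each component's control rate is at most 30%, and OR 1.56 describes a test that the analysis section does not plan. If 30% is meant for each outcome separately, the article does not say so.

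**Working it through.** **Inputs.** From the Sample size section: 350 participants allocated 1:1; 315, 284, 255 and 230 at the visits, or 157.5, 142, 127.5 and 115 per arm; alpha 0.025; power 0.80; control rate 30%; correlation ρ from 0.10 to 0.80. Assumptions, because the article is silent: two-sided alpha, exchangeable correlation, monotone dropout.

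**Method.** With m visits completed, a participant contributes m / (1 + (m − 1)ρ) units of information. Per arm, 115 people have four visits, 12.5 have three, 14.5 have two and 15.5 have one. At ρ = 0.10:

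I = 115×4/1.3 + 12.5×3/1.2 + 14.5×2/1.1 + 15.5 = 353.8 + 31.3 + 26.4 + 15.5 = 427.0

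The same sum gives I = 237.6 at ρ = 0.50 and 181.3 at ρ = 0.80.

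The detectable difference d = p1 − p0 solves d = (2.2414 + 0.8416) × √[(p0(1 − p0) + p1(1 − p1)) / I].

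**The plan's own figure.** The two stated effects agree: odds 0.30/0.70 × 1.56 = 0.6686, so p1 = 0.6686/1.6686 = 0.401, a difference of 0.101. At p0 = 0.30, p1 = 0.40 and ρ = 0.10, d = 3.083 × √(0.45/427.0) = 0.100, which is OR 1.556. A pooled variance gives 1.559 (0.101) and the log-odds scale 1.562 (0.101). The figure therefore reproduces at ρ of about 0.10. With the control rate still 30%, the detectable OR is 1.80 (13.5 points) at ρ = 0.50 and 1.95 (15.5 points) at ρ = 0.80. Other conventions shift the matching ρ without taking it out of the lower part of the range: one-sided alpha needs about 0.20, and two-sided alpha with first-order autoregressive correlation about 0.17 to 0.18.

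**Other control rates.** These rates are assumptions; the article gives none for the separate outcomes.

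| Control rate | Detectable OR, ρ 0.10 | Difference, ρ 0.10 | Detectable OR, ρ 0.80 |
|---|---|---|---|
| 3% | 2.71 | 4.7 points | 4.08 |
| 10% | 1.87 | 7.2 points | 2.49 |
| 20% | 1.64 | 9.0 points | 2.08 |
| 30% | 1.56 | 10.0 points | 1.95 |
| 50% | 1.53 | 10.4 points | 1.92 |

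As the control rate falls from 50%, the detectable OR rises and the detectable difference shrinks. The remark about power being lowest near 50% is therefore right for an absolute difference and wrong for an odds ratio, yet the section reports both.

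**If 30% is the combined rate.** Assume for illustration that the two outcomes are independent and PrEP is 3%. MOUD is then 1 − 0.70/0.97 = 27.8%, with a detectable OR of 1.57 (ρ 0.10) to 1.97 (ρ 0.80). MOUD is barely affected; PrEP moves to 2.71 to 4.08.

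**Splitting alpha.** Give each test 80% power at 0.025 (drift 3.083) and let the test statistics correlate 0 to 0.5. With fixed 0.025 each, the chance of winning both is 64% to 69%. With Holm (smaller p-value at 0.025, then the other at 0.05) it is 75% to 78%, and per-outcome power rises from 80% to about 85%. The chance of at least one win is 96% to 91% under either rule. Family-wise error is at most 0.05 under both.

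**The case against.** The operative analysis is fairly clear. The Abstract and Outcomes section use the plural, Table 1 separates the outcomes, and splitting alpha makes sense only for two tests. The sample size uses 0.025, the level of those tests, so 30% may well be meant for each outcome, and OR 1.56 would then apply to each. This favours the two-outcome reading and suggests that either win suffices. It does not settle the matter: no sentence states the success rule, and the formal hypothesis line and the objective still name one proportion.

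A reader might infer that the trial is badly underpowered for PrEP. Power for OR 1.56 at 3% control and ρ = 0.10 is indeed only about 15%, but that is a rise from 3.0% to 4.6%. For the 0.101 difference that the same section states, power at 3% control exceeds 99% at ρ = 0.10 and is about 91% even at ρ = 0.80. The 0 to 3% range also describes people who inject drugs generally. This control arm has active referral and an accompanied first clinic visit, and recruitment includes people who are interested in PrEP or MOUD. The article does not present 3% as its expected control rate.

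A reader might also take the 0.025 split as a mistake. It is a valid Bonferroni correction, and Holm does not raise the chance of at least one win.

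Finally, tables of detectable effects by outcome can be left to a fuller document. What cannot be left is which outcome the one printed figure belongs to.

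**Conclusion.** The point holds as an inconsistency in the primary hypothesis, together with a detectable effect that is not attached to either planned test. The arithmetic behind OR 1.56 is sound for one binary outcome at 30% control with ρ of about 0.10, the favourable end of the stated range. It becomes 1.80 to 1.95 at ρ of 0.50 to 0.80. If control PrEP engagement is below 30%, the figure does not apply to the PrEP test; the size of the shift (OR 1.64 at 20%, 1.87 at 10%, 2.71 at 3%, all at ρ = 0.10) rests on control rates assumed here. The documents do not support a conclusion that the trial is inadequate for PrEP, or that its alpha control is wrong.

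**What to change.** 1. Reword the objective and Hypothesis 1 as two hypotheses, one for PrEP and one for MOUD, and state that success on either is sufficient. If the combined proportion is wanted, name it as a secondary outcome.
2. Carry the same naming into the per-visit contrasts, the sex interaction and the futility rule.
3. In the Sample size section, give for each outcome a control rate, the correlation used, and the detectable OR and difference. Limit the remark about 50% to absolute differences.
4. Optionally, replace 0.025 for each test with Holm: the smaller p-value at 0.025 and, if that is significant, the other at 0.05.

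The cost is wording and two short calculations before data lock, with no added participants or data. Item 4 is a free gain in efficiency, not a correction.
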